## Methods

### Study design

This study will be performed in two stages. Stage I consists of the cluster-randomised clinical trial, and Stage II will be the process evaluation of the implementation of the CCDSS in the HMR service. Stage I will be conducted as a two-arm, parallel group, cluster-randomised clinical trial, with the cluster assignment occurring at the level of the ACP (Fig. 2). Stage II will use quantitative and qualitative research (mixed-methods process evaluation) to evaluate the process of the intervention within HMR. Stage II will run alongside (in parallel to) Stage I.

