The three tools within G-MEDSS will assist users to incorporate the patient’s goals, perspectives on deprescribing medications and their DBI score, together with their recommendations from their medication review, allowing a patient-centred approach to medication management. The G-MEDSS deprescribing report includes a combination of the results from the three tools: the person’s global goal of care, goals and strategies to improving the medication regimen, a summary of the patient’s current medications, the patient’s DBI score and information about interpreting the DBI, information about the rPATD, and a summary of the patient’s responses to the rPATD. The G-MEDSS system also allows ACPs to enter medication recommendations and actions on the G-MEDSS reports to allow for the GP to comment on deprescribing recommendations. The G-MEDSS system can create a patient/carer summary report for patients or their carers at the time of the HMR. The CCDSS format of G-MEDSS allows for the patient information to be easily and accurately captured, recorded and translated to a standardised report format, which can be adapted to most patient settings. The specifics of the intervention in this study will involve ACPs producing G-MEDSS reports about their HMR patients to send together with the HMR report (i.e. as part of Step 3, Fig. 1) to the patient’s GP, and providing the patient/carer G-MEDSS reports to the patients or their carers. ACPs in the comparison group will conduct HMRs for their patients without using the G-MEDSS system (usual care).

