#### Outcomes and follow-up

The primary outcome will be any reduction of anticholinergic and/or sedative medication use, as measured by DBI, between baseline and 3-months (binary outcome). Previous studies consistently observe an association between increasing DBI and impaired physical function [29]. The degree of exposure that results in a clinically significant change has been estimated to be a difference in DBI of approximately 0.5 [44]. Our previous study found that DBI is reduced in usual care HMR in 8.9% of patients by a median value of 0.28 [45], and an increase in this proportion by 10% was seen as a clinically meaningful effect on a population level. It was not feasible to power the study to primarily investigate impact on multifactorial measures of physical function.

Secondary outcomes will include:
Recommendations to reduce anticholinergic and or sedative medications as measured by DBI in the HMR report and/or the G-MEDSS report;Prevalence of deprescribing (cessation and/or dose reduction) any medicationChanges in clinical outcomes (physical function, cognitive function, falls, and institutionalisation)Changes in patient process outcomes (medication adherence and physician visits)Mortality at 3-monthsA subgroup analysis (of the above outcomes) for people living with and without dementia

All ACPs will be required to collect additional information of their HMR recipients at baseline (during HMR interview) and at a 3-month follow-up visit. The 3-month follow-up has been added exclusively to this study for the purposes of data collection as the HMR process (usual care) does not involve a follow-up visit. The following outcomes will be assessed of the patient participants enrolled in the study: medication adherence, cognitive impairment, functional status, falls, institutionalisation and the number of physician visits. Mortality data will be captured by the ACP participants at 3-month follow-up (Table 1).

**Table 1 Tab1:** Patient participant data to be collected during the study

	Measure (s)	Baseline^a^	3-months
Demographics			
Age		✓	
Sex		✓	
Ethnicity		✓	
Marital Status		✓	
Education Status		✓	
Geographic remoteness/locality	PhARIA	✓	
Medication Profile			
Current medication list (prescribed, OTC and complementary, regular or PRN)		✓	
Changes to medication list (e.g. additions, cessations, ↑↓dose)			✓
Ceased medications		✓	✓
Adherence	MGL	✓	✓
Attitudes towards deprescribing^b^	rPATD, rPATDCog	✓	
Anticholinergic and sedative burden	DBI	✓	✓

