Comorbidity and Physical Function			
Comorbidities	FCI	✓	✓
Cognition	Mini-Cog© [46]	✓	✓
Independent activities of daily living	NHCCSFSI	✓	✓
Physical Function	SPPB	✓	✓
Falls History		✓	✓
Others			
Institutionalisation (e.g. hospitalisation)		✓	✓
Physician visits (e.g. GP or specialist appointments)			✓
Mortality			✓
Goals of care^b^		✓	

^a^at the time of the HMR interview; ^b^only for patients in the intervention arm of the study

*PhARIA* The Pharmacy Access/Remoteness Index of Australia – quantifies degree of remoteness (geographic and professional) [47], *OTC* Over-the-counter, *PRN* when required, *MGL* Morisky, Green, Levine Scale [48], *rPATD* revised Patients’ Attitudes Towards Deprescribing [34], *rPATDCog* Revised Patients’ Attitudes Towards Deprescribing for people with Cognitive impairment [35], *DBI* Drug Burden Index [28], *FCI* Functional Comorbidities Index [49], *NHCCSFSI* National Home and Community Care Services Functional Screening Instrument [50], *SPPB* Short Physical Performance Battery [51], *GP* General practitioner

↑↓ = changes

The Morisky Green Levine Scale will be used to measure self-reported patient medication adherence [48]. Cognitive impairment will be assessed using the Mini-Cog© [46, 52–54]. The National Home and Community Care services Functional Screening Instrument (NHCCSFSI) (part one) and the Short Physical Performance Battery (SPPB) will be used to assess the functional status of patient participants [50, 51]. Details regarding scoring of these measures used in this study can be found in Additional file 1.

Data to calculate the Functional Comorbidity Index (FCI) will be collected from the patients. The FCI is a sum of 18 self-reported comorbid conditions with a score of 0–18. The FCI will also be used to measure comorbidities that predict physical function in older adults. A higher FCI score indicates greater morbidity and is associated with poorer physical function [49].

Falls (any fall in the last 12 months at baseline and number of falls at 3-months), institutionalisation (admission to hospital in the last 12 months at baseline and number of days admitted to hospital, nursing home or respite care at 3-months) and the number of physician visits (GP and specialist) will be captured over 3 months by providing patients and/or their carers a calendar to self-record events that will be collected by ACPs.

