#### Statistical analyses

The primary analyses will be conducted using an ‘intention-to-treat’ approach and will be reported according to the guidelines of the Consolidated Standards of Reporting Trials (CONSORT) 2010 statement. Descriptive statistics (means and proportions) will be used to report the demographics of the study populations (ACPs and patient participants) at baseline. Binary continuous and count outcomes will be analysed using logistic, linear and negative binomial regression models, respectively. All models will include a covariate for the intervention group, with a random effect for the clusters (ACPs). Analyses will provide an estimate of the difference between groups, 95% confidence intervals (CI) and *p*-values. All statistical tests will be two-tailed, and p-values of < 0.05 will be deemed statistically significant. Appropriate model checking will be conducted. The statistician performing the data analysis will be blinded to the identity of each treatment group.

Secondary analyses will include:
Where appropriate, to conduct further adjusted analyses, covariates will be included for the patients’ baseline value (for that outcome) and any baseline characteristic for which there is evidence of imbalance between intervention and comparison groups;A subgroup analysis for people living with dementia;For clinical outcomes, assessments of associations between change in DBI or a deprescribing of a medication, using the same statistical methods as described above, but with the intervention group removed from the model and replaced by change in DBI or deprescribing of medication;Association between rPATD and deprescribing in overall patient population.

To analyse the responses to the rPATD questionnaire, factor scores will be created for each of the 4 factors (appropriateness, burden, concerns about stopping and involvement) as previously described [34]. Likert responses to the global question ‘I would be willing to stop one or more of my medications if my doctor said it was possible’ will be dichotomised into those that agree (strongly agree and agree) and those that are unsure/disagree (unsure, disagree, strongly disagree). Factor scores and responses to the global questions will be compared to deprescribing outcomes (DBI and prevalence of deprescribing) using Mann-Whitney and χ^2^ tests.

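### The rPATD–deprescribing association is planned for the whole trial population, but rPATD is collected only in the intervention arm; the tests named for it also ignore clustering by pharmacist, with a probably small effect

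*Protocol article*

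**What the plan says.** Under Statistical analyses, the last item in the list of secondary analyses is "Association between rPATD and deprescribing in overall patient population". The paragraph after the list explains how rPATD is to be handled. Four factor scores are formed, the global willingness item is split into agree versus unsure or disagree, and these "will be compared to deprescribing outcomes (DBI and prevalence of deprescribing) using Mann-Whitney and χ^2^ tests".

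Under Outcomes and follow-up, the relevant row of Table 1 reads "Attitudes towards deprescribing^b" and is ticked at baseline only. Footnote b to that table means "only for patients in the intervention arm of the study".

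The Intervention section agrees with the footnote. It lists rPATD as one of the three G-MEDSS tools, says that a summary of the patient's answers goes into the G-MEDSS report sent to the GP, and adds that "ACPs in the comparison group will conduct HMRs for their patients without using the G-MEDSS system (usual care").

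On clustering, the Study design section describes a cluster-randomised trial "with the cluster assignment occurring at the level of the ACP". Statistical analyses says of the regression models: "All models will include a covariate for the intervention group, with a random effect for the clusters (ACPs"). The rPATD paragraph states no adjustment for clusters.

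**The concern.** There are two separate problems, and the first matters more.

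**Population.** An analysis described as covering all patients needs rPATD from all patients, and Table 1 says that half of the trial will not have it. The difference also affects interpretation. In the arm that has data, the GP is sent the patient's attitudes towards deprescribing. An association there may arise because willing patients are deprescribed more, or because the report itself prompts the GP. It does not describe how attitudes relate to deprescribing under a usual-care review, and the overall label invites that use.

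**Clustering.** The standard Mann-Whitney and chi-squared tests assume independent patients. The plan itself assumes that DBI reduction is correlated within pharmacist. If rPATD answers are also alike within pharmacist, for instance because of how a pharmacist presents the questionnaire, these tests give p-values that are somewhat too small. If the answers do not cluster, there is essentially no distortion.

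**Working it through.** **1. Population, with the sections set side by side.**
- Statistical analyses: the association is planned in the overall population.
- Table 1, rPATD row and footnote b: intervention arm only.
- Intervention: rPATD is part of G-MEDSS; the comparison arm works without G-MEDSS.
- Statistical analyses, free-text goals: the other Table 1 row carrying footnote b is goals of care, and there the analysis is expressly limited to the intervention arm. The restriction was carried through for one footnote-b item and not for the other.

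Number with data: the Sample size section plans 500 patients, an average of 5 per ACP, and equal numbers of ACPs per arm. That is 500/5 = 100 ACPs, 50 per arm, and 50 × 5 = 250 patients with rPATD.

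**2. The plan's own figure, to confirm the clustering inputs.** Inputs from Sample size: 20% versus 10%, two-sided 5%, 80% power, ICC 0.07, average cluster size 5.
- Design effect = 1 + (5 − 1) × 0.07 = 1.28.
- Per arm before clustering (unpooled variance): (1.96 + 0.8416)² × (0.20 × 0.80 + 0.10 × 0.90) / 0.10² = 7.849 × 25 = 196.2, so 197. The pooled-variance form gives 199.
- Total: 2 × 197 × 1.28 = 504, or 2 × 199 × 1.28 = 509.
- Power at 250 per arm is 79.3%.

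The stated 500 is reproduced to within 2%, so the plan does rest on ICC 0.07 and a design effect of 1.28 for DBI reduction.

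**3. True level of a test that ignores ACP.** For a predictor that varies between patients, the variance inflation is approximately

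inflation = 1 + (m − 1) × ICC(outcome) × ICC(rPATD),

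and the true two-sided level of a nominal 5% test is 2 × [1 − Φ(1.96 / √inflation)]. Put m = 5 and ICC(outcome) = 0.07, so that (m − 1) × ICC(outcome) = 0.28. The document gives no ICC for rPATD, so a range is shown.

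| ICC of rPATD (assumed) | Inflation | True level |
|---|---|---|
| 0 | 1.000 | 5.0% |
| 0.1 | 1.028 | 5.3% |
| 0.2 | 1.056 | 5.7% |
| 0.5 | 1.140 | 6.6% |
| 1 (upper bound) | 1.280 | 8.3% |

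**4. Check by simulation.** A chi-squared test was simulated with 50 clusters of 5, outcome 20% with ICC 0.07, and 70% willing (the Background cites 60–80%), at 20,000 runs per setting. The rejection rates were 5.3%, 5.6%, 5.6%, 6.8% and 8.5% at rPATD ICC 0, 0.07, 0.2, 0.5 and 1. The 5.3% at ICC 0 cannot come from clustering, so differences of about 0.3 points from the formula should not be read as meaningful. Only the chi-squared test was simulated; for Mann-Whitney the formula is taken as an approximation.

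**The case against.** **Overall may mean patients with and without dementia together.** The dementia subgroup stands two items earlier in the same list, so this reading is possible. The text does not say it, however, and the words still conflict with footnote b. On this reading the remedy is the same: name the arm.

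**Nothing shows that the result would be misreported.** This is fair. The protocol does not say how the finding will be presented, and footnote b openly states the restriction. A reader might infer that the authors intend to attribute an intervention-arm result to all HMR patients; the document does not support that inference. What stands is that the stated population cannot be analysed.

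**No sample size was claimed for this analysis.** Also fair. A reader might infer that 500 patients were promised for the rPATD association. The Sample size section ties 500 to the primary DBI comparison only, so 250 describes the data available and corrects no stated figure.

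**The clustering effect is small.** This largely stands. A reader might take 8.3% as the level to expect, but it requires every patient of one ACP to give the same rPATD response, which is unlikely for a questionnaire on individual attitudes. Under weak to moderate clustering the level is about 5–6%. The ICC of 0.07 comes from the DBI feasibility study, and applying it to deprescribing of any medication is a further assumption. It remains true that the tests depart from the approach used for the plan's models.

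**Conclusion.** The point holds as a minor one. The planned rPATD analysis cannot be carried out in the population named for it. It can be carried out in the intervention arm, in about 250 patients at planned recruitment and before losses, and its result applies only there, where the rPATD summary is itself part of what the GP receives.

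The unadjusted tests are a secondary weakness. The true level is about 5.0–5.7% for an rPATD ICC of 0 to 0.2, 6.6% at 0.5, and at most 8.3%. These figures assume 5 patients per ACP, an outcome ICC of 0.07, and an rPATD ICC that the document does not supply.

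A reader might infer that the trial's main conclusion is at risk. It is not: this is the last-listed secondary analysis, it is observational, and it touches neither the primary outcome nor the randomised comparison.

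**What to change.** 1. In the list of secondary analyses, name the intervention arm as the population for the rPATD association, and report the result as an intervention-arm finding. If the authors meant patients with and without dementia together, say so as well.
2. Replace the Mann-Whitney and chi-squared tests with the logistic mixed model of the same section. The outcome is DBI reduction or any deprescribing, the rPATD factor score or dichotomised global item takes the place of the intervention term, and the ACP random effect is kept. The plan already makes this kind of substitution for clinical outcomes in the item just before. Adjustment for baseline DBI is optional.

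The cost is two sentences of wording and no new data. Collecting rPATD in both arms and amending footnote b would also remove the contradiction. It would, however, bring a G-MEDSS tool into usual care, and the protocol does not address what that would do to the comparison, so it is not requested here.

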Clinicians have increasingly been encouraged to involve patients in the clinical decision-making process. In 2001, The United States Institute of Medicine defined patient-centred care as ‘care that is respectful of and responsive to individual patient preferences, needs and values’. [32] Recent studies on deprescribing have stressed the importance of identifying patients’ preferences, patient involvement and shared-decision making [33]. The revised Patients’ Attitudes Towards Deprescribing (rPATD) questionnaire explores peoples’ attitudes, beliefs, and experiences regarding the number of medications that they are taking and how they would feel about ceasing one or more of their medications [34]. This questionnaire identifies the barriers and enablers to deprescribing inappropriate medications at the individual patient level, is reliable, and has been validated in older patients, caregivers and people living with mild cognitive impairment and mild-to-moderate dementia (rPATDCog) [35]. The development of the rPATDCog demonstrated a strong agreement between responses from people living with cognitive impairment and their carers [35]. In recent studies, 60–80% of older adults and caregivers were willing to have a medication deprescribed if their doctor said it was possible [36, 37]. To date, the rPATD has not been trialled as a tool to guide deprescribing in a clinical setting.

Discussing the goals of care with older adults may help healthcare practitioners incorporate the concerns and wishes of patients when making decisions [38]. Goals of care are particularly important for people living with dementia, as dementia and its related comorbidities may be multifactorial, and goals of care may be less clear and less well articulated than for people without dementia [39]. Identifying and discussing goals of care during a HMR has the potential to guide prescribers in choosing appropriate treatment or care options for the individual.

We hypothesise that the combination of pharmacist-led medication review (HMR) and a CCDSS intervention that incorporates validated deprescribing tools and patient-centred guides may reduce the proportion of older adults using anticholinergic and sedative medications and improve clinical outcomes in community-dwelling older adults.

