##### Intervention

The Goal-directed Medication review Electronic Decision Support System (G-MEDSS) (accessible from gmedss.com) is a validated electronic platform (CCDSS) that has been designed to provide clinical decision support for healthcare practitioners (GPs and ACPs) when completing a medication review for their older patients, to provide person-centred care to meet their goals and preferences. The G-MEDSS platform was, developed, validated and evaluated in a previous study with ACPs, GPs and carers for people living with dementia, using mixed-methodology that informed the design and usability of the tools within the CCDSS [42]. The G-MEDSS is designed to produce patient-specific deprescribing reports for a patient’s GP.

The G-MEDSS contains three tools:
The Goals of Care Management tool allows the patient’s goals of care to be identified and aligned with their medication management strategies. The tool also allows for free-text information to be entered into the system.The Drug Burden Index Calculator© is a validated tool that identifies medications with anticholinergic and sedative effects (measured by the DBI) and provides information on a patient’s total exposure to these drug classes and their risks to older people [28, 31].The revised Patient’s Attitudes Towards Deprescribing questionnaire (rPATD) was developed and validated to explore people’s attitudes, beliefs, and experiences regarding the number of medications that they are taking, and how they would feel about ceasing one or more of their medications [34, 43]. Three different versions of the rPATD were incorporated into G-MEDSS to allow for selection as appropriate for the patient: a) older adult, b) caregiver, and c) people with cognitive impairment (rPATDcog) versions [35]. The psychometric properties of the rPATD were established in Australian older adults and carers, and has established face, content, criterion, construct and internal validity and test-retest reliability.

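### The rPATD–deprescribing association uses unadjusted tests across three questionnaire versions, so it cannot separate attitude from version and ignores clustering by pharmacist

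*Protocol article*

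**What the plan says.** The Intervention section says: "Three different versions of the rPATD were incorporated into G-MEDSS to allow for selection as appropriate for the patient". It lists them as "a) older adult, b) caregiver, and c) people with cognitive impairment (rPATDcog) versions". Version therefore follows who answers and the patient's cognitive status.

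Statistical analyses gives one scoring sentence: "factor scores will be created for each of the 4 factors (appropriateness, burden, concerns about stopping and involvement) as previously described [34"]. The footnote to Table 1 (Outcomes and follow-up) attributes the cognitive version to another source: "Revised Patients’ Attitudes Towards Deprescribing for people with Cognitive impairment [35"]. The scoring sentence does not cite that source.

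The planned secondary analysis is "Association between rPATD and deprescribing in overall patient population". The factor scores and the dichotomised willingness item "will be compared to deprescribing outcomes (DBI and prevalence of deprescribing) using Mann-Whitney" and chi-square tests. No stratum or covariate is named. The same section gives its regression models a random effect for pharmacists, but these tests are not regression models.

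A footnote to Table 1 says that the rPATD is collected "only for patients in the intervention arm of the study". The overall population for this analysis can therefore only be the intervention arm.

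**The concern.** In their standard form, Mann-Whitney and chi-square tests compare two groups of independent patients. They have no place for version and none for pharmacist.

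Version could act as a confounder. A caregiver answers about someone else's medicines, and the cognitive version marks impaired cognition. The Background says that people with dementia are prescribed more medicines and are especially sensitive to adverse events from CNS-acting drugs, so their chance of deprescribing may differ whatever their attitude. If score levels also differ by version, a comparison across versions can show an association that exists within none of them, or shift a real one.

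The Background also notes that the rPATD has not yet been trialled as a clinical guide to deprescribing, so readers may take an interest in this result even though it is secondary.

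**Working it through.** The article gives no figure for this analysis, so there is none to reproduce. The check asks how large the distortion could be.

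**Inputs from the article**
- Patients: 500 planned, so about 250 in the intervention arm if split equally.
- Dementia: 10–31% expected, a rough proxy for use of the caregiver or cognitive version. That is 25 to 78 of 250.
- Pharmacist clusters: average 5 patients, ICC 0.07.

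**Assumed inputs (not in the article)**
- 25% answer the caregiver or cognitive version (the minority versions).
- Willingness is 80% on the older-adult version and 60% on the others.
- Deprescribing is 20% on the older-adult version and either 35% or 10% on the others.
- Willingness and deprescribing are unrelated within each version.

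**Pooled odds ratio**
- Willing: 0.75 × 0.80 + 0.25 × 0.60 = 0.60 + 0.15 = 0.75. Not willing: 0.15 + 0.10 = 0.25.
- Deprescribing 20% v 35%. Among the willing: (0.60 × 0.20 + 0.15 × 0.35)/0.75 = 0.230. Among the rest: (0.15 × 0.20 + 0.10 × 0.35)/0.25 = 0.260. Odds ratio = (0.230/0.770)/(0.260/0.740) = 0.85.
- Deprescribing 20% v 10%. Among the willing: (0.12 + 0.015)/0.75 = 0.180. Among the rest: (0.03 + 0.01)/0.25 = 0.160. Odds ratio = (0.180/0.820)/(0.160/0.840) = 1.15.
- Letting the minority share run from 15% to 40%, and adding a 15% v 30% deprescribing contrast, gives 0.81 to 1.20.

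**Against sampling error at n = 250**, with SE(log OR) = √(sum of 1/cell count):
- First case, cells 43.1, 144.4, 16.3 and 46.3: SE = 0.34. The bias is |ln 0.85|/0.34, about 0.48 SE.
- Second case, cells 33.8, 153.8, 10.0 and 52.5: SE = 0.39. The bias is ln 1.15/0.39, about 0.36 SE.
- The 95% interval spans a factor of about 1.9 to 2.2 either side (e^(1.96 × SE)).

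**Factor scores, by simulation.** Settings: n = 250, two respondent groups, 20% deprescribing among self-respondents, no association within group, 5% two-sided test, 1,500 runs per setting.

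| Setting | Pooled test, false positives |
|---|---|
| Groups differ in score only or in deprescribing only | about 4–6% |
| Both differ, minority share 10% | about 5–9% |
| Both differ, minority share 31% | about 7–21% |

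Score shifts were 0.5 or 0.8 SD, and minority deprescribing was 10%, 30% or 40%. The 21% comes from the most extreme setting (31% share, 0.8 SD, 40% v 20%). A rank test stratified by version stayed at about 4–6% throughout.

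**Clustering.** With 5 patients per pharmacist and ICC 0.07, the design effect is 1 + (5 − 1) × 0.07 = 1.28, or √1.28 = 1.13 on the standard error. That full inflation applies only if all patients of one pharmacist share the same attitude score. For scores that vary between patients it is smaller.

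**The case against.** The strongest reply is that a reader might infer a stated plan to pool all versions under one scoring, and the article never says that. Pooling is inferred from the single scoring citation and the overall-population wording. The cited source is not available here. The Intervention section says that the psychometric properties were established in both older adults and carers, so that source may already score those two separately. Version-specific scoring may also sit in the full protocol or analysis plan. This stands, and it limits the scoring part of the point to a request that the rule be stated. It does not rescue the tests: the article names them, and neither adjusts for version or for pharmacist.

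A reader might also take "60–80% of older adults and caregivers were willing to have a medication deprescribed" as evidence that caregivers and older adults differ. It is one range across studies covering both groups, not a contrast between versions. The 80%/60% split above is an assumption, and so are the deprescribing rates.

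The Background reports strong agreement between people with cognitive impairment and their carers. This is a partial mitigation, but it does not compare cognitively intact older adults with either group. The planned dementia subgroup does not cover the gap: in Outcomes and follow-up it applies to the listed outcomes, and the rPATD is not among them.

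Finally, separate estimates by version would be sparse. At 20% deprescribing, 25 to 78 minority-version patients give about 5 to 16 events across two versions. This stands and shapes the fix.

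**Conclusion.** The point holds as a weakness in a stated method. The named tests cannot distinguish attitude from respondent type and cognition, and they leave out the pharmacist clustering that the same section builds into its models.

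A biased result is possible but not demonstrated. It needs versions to differ in both score and deprescribing rate, and the article documents neither difference. On the assumptions shown, the false odds ratio is about 0.85 or 1.15, under half a standard error in about 250 patients. It would matter more with a large minority share and marked differences between versions. The article does not support the stronger inference that the planned analysis will produce a false association.

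The analysis is secondary. The primary outcome and the randomised comparisons are unaffected. Label: free improvement.

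**What to change.** Replace the Mann-Whitney and chi-square tests with a logistic model for each binary deprescribing outcome. The factor score or willingness item is the predictor, with a random effect for pharmacist and version (older adult, caregiver, cognitive impairment) as a covariate or stratum. If DBI change is analysed as continuous, use the linear counterpart that the section already provides for.

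State how each version is scored, citing its own validation source. A covariate removes differences in level but not in scale, so if the scoring ranges differ, put scores on a common scale within version first. Report results by version descriptively, where numbers allow. Say that the analysis population is the intervention arm.

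The cost is a change of analysis wording. Version is selected inside G-MEDSS, so it should be recoverable, but the team should confirm that it is recorded and exported. Recruitment and patient visits do not change.
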